**BACKGROUND**

Postural disorders in Parkinson's disease fit into the context of a general axial involvement , with a negative influence on balance and gait resulting in a significant worsening impact on quality of life . Some authors have described the various mechanisms involved in the development of these alterations and reported that there are multiple mechanisms that play an key role in the development of these postural disorders. In particular seems that there is a disintegration of proprioceptive information with a critical role of sensory information at different level of CSN with an impairment in kinesthesia. The aim of this pilot study is to verify whether a rehabilitation approach that involves the use of a device proprioceptive ( Equistasi ) is more effective than single traditional physiotherapy for postural deformities and postural instability. We believe that the use of this novel postural device(Equistasi) could balance and posture and that could help in maintaining long-term after the treatment . Equistasi is a Class I medical device CE mark issued by the Ministry of Health 30/10/2009 registered as a postural stabilizer . This is a device the size of 1 x 2 cm , composed exclusively of synthetic fibers coated with a shell of soft and flexible , non-toxic and CE marked , which is not powered by electric charges , no fibers deriving from metals , it is not chemical compound pharmacological , has no microchip inside. In contact with body temperature emits focal micromechanical vibrations that can not be perceived by the patient. Its action results in a stimulation of proprioception primarily via neuronal pathways that lead to the vibratory sensitivity (via spino- ponto - thalamic ) . Our hypothesis is supported by several studies demonstrating that in the neck there is a high concentration of proprioceptive receptors that are important for the maintenance of the head on the vertical line during upright standing position . It has also been demonstrated that patients may have a deficit in the perception of one's body position ,confirmed by the fact that the perception of horizontal and vertical position in patients with Parkinson's disease is characterized by a deviation in lateral bending. The study will use this postural stabilizer device ( Equistasi ) in association with a physiotherapy program for balance and posture because it seems to stimulate the proprioceptive information , thanks to the special composition of microfibers that emit micromechanical vibrations . The use of the latter has led, in recent studies , a number of positive effects in stimulating muscle proprioception and specifically on the use of focal mechanical vibratory stimulation in Parkinson's disease .

**OBJECTIVE**

The objective of this preliminary study is:

- to verify if the proposed device (Equistasi) as a proprioceptive postural stabilizer may represent an innovative and effective treatment in association with a physiotherapy program in improving balance and posture alterations and in maintenaning the outcome

-verify if the improvement obtained on postural perturbations have a positive effect on postural stability and falls in PD.

**STUDY DESIGN**

The study is expected to enroll approximately 36 patients; they will be randomized into one of the following groups :

1 . 18 patients Experimental Group E-PT ( Equistasi + Physical Therapy )

2 . 18 patients Group Control P -PT ( Placebo + Physical Therapy)

The two groups will submitt to the following programs :

Group 1 E-PT : physiotherapy program plus the innovative postural stabilizer device ( Equistasi ) for 8 weeks with a training balance program which includes exercises for balance training, postural realignment , muscle strengthening.

Equistasi will be applied on the skin with a duration ranging from a minimum of one hour to a maximum of four hours per day, gradually increasing the duration of application every week.

Group 2 P -PT : similar physiotherapy treatment plus an inactive device (placebo) , of the same duration and frequency of the first group . It will be used in the form of a placebo device similar to 'Equistasi but inactive.

**PARTICIPANTS ELIGIBILITY**

INCLUSION CRITERIA**:**

- Patients admitted to the U. O.S. Neurorehabilitation FBF Venice

- Parkinson's disease staged II-III H & Y

- Presence of postural alterations

- Presence of postural instability

- Ability to participate in a physiotherapy venue

- Absence of cognitive impairment (MMSE> 24/30)

- Stable medications

EXCLUSION CRITERIA:

- Presence of DBS

- severe cardiac and / or pulmonary disease

-Unstable medication

**STATISTICAL ANALYSIS**

They will be subjected to statistical analysis of the data derived from the stabilometric , posturographic evluation , as well as those from clinical scales . This clinical trial will use a sample of convenience, with the assumption that 40 participants would be ample to explore safety and feasibility. Given the small sample and the lack of normal distribution of most of the variables on Shapiro-Wilk test, non-parametric statistics will use. Initially, The data will be subjected to statistical analysis ANOVA in order to produce an analysis of variance univariate and then to test the hypothesis of equality of more medium .
A comparison will be made for all variables (extrapolated data from rating scales , posturographic test , and baropodometry stabilometry ) and for dependent samples for independent samples to evaluate both the variation within the group than those between the two groups. This will be done through the use of a T- test .
The number of patients included in the study is the minimum number to conduct a pilot study to have a statistical significance level . Patients will undergo randomization criteria following the Conshort Procedures for radomization.

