**METHODS**

The following evaluation forms , questionnaires and instrumental evaluation will be administered at the beginning of treatment to all patients in all groups :

- Measurement of the angle of inclination of the trunk, using markers placed on specific points of reference on the basis of criteria established by analyzing posturographic

- Measurement of the position of the center of mass (COM) through data extracted from platform to baropodometry

- Stabilometry to evaluate the COP displacement in static and instrumental FRT

- Berg Balance Scale to assess balance

- Diary of falls and FES (Fall Efficacy Scale) to monitor falls rate and fear of falling

- PDQ -39 to assess the quality of life

- UPDRS (II -III section ) to assess motor disability

These instrumental tests , clinical evaluation will be administered again at the end of the eight weeks of treatment, rehabilitation and after another eight weeks of follow up.

Duration of the research

For each patient, an initial assessment will be performed T0, another evaluation after 8 weeks of treatment T1 and a final evaluation T2 after 8 weeks. The duration of the research study for each patient was then 16 weeks.

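### No stated between-arm analysis adjusts for the T0 value or models T1 and T2 together, although every measure is taken at all three visits

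*Protocol*

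**What the plan says.** The Study Design section of the Protocol describes two randomised arms: "The study is expected to enroll approximately 36 patients", with 18 in each. Both arms receive physiotherapy, one with the active device and one with an inactive device.

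The Methods section sets the visits: "an initial assessment will be performed T0, another evaluation after 8 weeks of treatment T1 and a final evaluation T2 after 8 weeks". The full list of instrumental tests, scales and the falls diary is given at the start and repeated at both later visits.

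The Statistical Analysis section names two steps:

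- First, an "analysis of variance univariate and then to test the hypothesis of equality of more medium". No factor, visit or covariate is named.
- Then, for all variables, comparisons "for dependent samples for independent samples to evaluate both the variation within the group than those between the two groups". On the method: "This will be done through the use of a T- test".

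The section mentions no T0 covariate and no arm-by-visit term. It does not say whether the between-arm test compares follow-up values or changes from T0.

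**The concern.** The Objective section asks whether adding the device to physiotherapy improves balance and posture, and whether the gain lasts. Only a comparison between arms, at T1 and at T2, can answer that. The named tests serve it poorly in three ways.

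- **The ANOVA adds nothing between arms.** With two groups, the one-way F statistic equals t squared, so it is the same test as the independent t-test.
- **The paired tests answer another question.** They show whether patients within one arm changed. Both arms receive physiotherapy, so both may improve whatever the device does.
- **The independent t-test is not said to use T0.** With 18 per arm, chance differences at T0 will be common. If follow-up values alone are compared, these differences carry into the estimated device effect, and the precision that T0 offers is lost.

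At stake are precision in a small trial and the risk that the device is judged by which arm's paired test reaches significance.

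**Working it through.** **Inputs.** From the Protocol: 18 patients per arm, two arms, visits T0, T1 and T2. Assumed, because the Protocol gives none of them: two-sided 5% level, 80% power, equal SDs at T0 and follow-up, and a T0-to-follow-up correlation r of 0.5, 0.7 or 0.8. The Protocol has no power calculation or detectable difference to reproduce.

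**Step 1: variance of the between-arm difference**, relative to a t-test on follow-up values (set to 1):

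- t-test on change from T0: 2(1 − r)
- ANCOVA on T0: 1 − r²
- Reduction by ANCOVA against follow-up values: r²
- Reduction by ANCOVA against change: 1 − (1 − r²)/[2(1 − r)] = (1 − r)/2

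| Assumed r | Change score variance | ANCOVA variance | ANCOVA saves vs follow-up values | ANCOVA saves vs change |
|---|---|---|---|---|
| 0.5 | 1.00 | 0.75 | 25% | 25% |
| 0.7 | 0.60 | 0.51 | 49% | 15% |
| 0.8 | 0.40 | 0.36 | 64% | 10% |

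**Step 2: detectable difference.** At 18 per arm the noncentral t gives 0.961 SD for a t-test on follow-up values. Multiply by the square root of the relative variance:

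- ANCOVA: 0.961 × √0.75 = 0.83; 0.961 × √0.51 = 0.69; 0.961 × √0.36 = 0.58 SD.
- Change score: 0.961 × √1.00 = 0.96; 0.961 × √0.60 = 0.74; 0.961 × √0.40 = 0.61 SD.

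This scaling leaves out the small cost of estimating the slope on T0.

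**Step 3: power for an assumed effect of 0.8 SD** (34 degrees of freedom for the t-tests, 33 for ANCOVA):

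| Analysis | r = 0.5 | r = 0.7 | r = 0.8 |
|---|---|---|---|
| Follow-up values | 64.5% | 64.5% | 64.5% |
| Change from T0 | 64.5% | 85.3% | 95.8% |
| ANCOVA on T0 | 76.7% | 90.3% | 97.3% |

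**Step 4: chance imbalance at T0.** The standard error of the T0 difference is √(2/18) = 0.33 SD. A difference larger than one standard error arises by chance in about 32% of trials of this size.

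**Step 5: why the paired tests cannot stand in.** Suppose both arms improve equally by 0.5 SD with r = 0.7, so the device adds nothing. Each paired test then has about 73% power. The chance that exactly one arm is significant is 2 × 0.73 × 0.27 = 0.39.

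**The case against.** Several points on the other side are fair.

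- **The plan does use the repeated measurement in part.** A reader might infer that T0 and the pairing are ignored altogether. The text does not support that, because dependent-samples tests within each arm are planned. What is missing is their use between arms.
- **The between-arm test may be on changes.** The wording on variation within and between groups can be read that way. T0 would then be used, and the gain from ANCOVA is the smaller set of figures, 25% / 15% / 10%. The text does not settle this, so both sets are given.
- **An ANOVA across visits that treats the same patients as independent samples** is another tempting inference, and would be a real error. But no factor is named, a repeated-measures ANOVA also has a univariate form, and paired tests are planned alongside. The Protocol does not state the faulty version.
- **A loss of half the information** might also be inferred. No correlation is given. Half corresponds to r of about 0.71 with follow-up values only, and it is not a ceiling.
- **Covariates are often left to an analysis plan**, which is not at hand. That would be decisive if the Protocol were silent. Here it names the tests, and an analysis plan that followed it would inherit the weakness.
- **An unadjusted randomised comparison is valid**, and its standard error already allows for chance imbalance. This stands: the point is about efficiency, not bias.
- **A normal-theory model does not suit everything.** The same section expects non-normal data and refers to non-parametric statistics, and falls are counts. This limits the remedy but does not remove the point, since the usual rank tests between arms do not adjust for T0 either.

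**Conclusion.** The point holds as a matter of efficiency and clarity. The Protocol commits to between-arm tests that are not stated to use T0 or to model T1 and T2 jointly, although the data for both are collected. Against a t-test on follow-up values, ANCOVA on T0 cuts the variance by 25% to 64% for r from 0.5 to 0.8. Against a t-test on change, it cuts it by 25% down to 10% over the same range. Apart from one degree of freedom and the small cost of estimating the slope, ANCOVA is at least as efficient as either.

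These sizes rest on an assumed correlation, equal SDs at T0 and follow-up, and 18 per arm. The percentage reductions do not depend on the sample size. The Statistical Analysis section speaks of a "sample of convenience, with the assumption that 40 participants would be ample to explore safety and feasibility". At 20 per arm the starting detectable difference is 0.91 rather than 0.96 SD, and the same proportions apply. The planned tests are not invalid, but a better analysis is available from data already planned.

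**What to change.** In the Statistical Analysis section:

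1. For continuous and scale outcomes, make the between-arm analysis an ANCOVA with arm and the T0 value, at T1 and at T2. Equivalently, use one repeated-measures model with arm, visit, arm-by-visit and T0.
2. Report the adjusted between-arm difference at each visit with its 95% confidence interval.
3. Use a rank-based or transformed version where the distribution requires it, and a count model for falls.
4. Keep the paired within-arm tests as descriptive only, and drop the ANOVA that repeats the t-test.

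No new data are needed, since T0 is already planned for every listed measure. The cost is one degree of freedom for the covariate and slightly more analysis work, including the choice of model for the non-normal outcomes.

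### No primary outcome or visit is named although every variable is to be tested, so a claim for the device could rest on any one of about 20 between-arm comparisons

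*Protocol*

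**What the plan says.** Protocol, STATISTICAL ANALYSIS, sets the testing rule: "A comparison will be made for all variables", covering rating scales, posturography, baropodometry and stabilometry. The purpose is "to evaluate both the variation within the group than those between the two groups", and "This will be done through the use of a T- test". An ANOVA is to come first, and non-parametric methods are also announced. The section gives no alpha. It says only that the number of patients is the minimum for a pilot study "to have a statistical significance level".

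Protocol, METHODS, lists the trunk inclination angle, centre-of-mass position, static COP displacement, instrumental FRT, Berg Balance Scale, falls diary, FES, PDQ-39, and UPDRS sections II and III. These "will be administered again at the end of the eight weeks of treatment, rehabilitation and after another eight weeks of follow up", which gives visits T1 and T2 after the baseline T0.

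Protocol, OBJECTIVE, asks whether the device "may represent an innovative and effective treatment in association with a physiotherapy program in improving balance and posture alterations". It adds maintenance of the result, and effects on postural stability and falls. BACKGROUND asks whether adding the device is more effective than physiotherapy alone. No section names a primary outcome or a primary time point.

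**The concern.** The question is one of efficacy and the tool is the significance test, but nothing says which test answers the question. All measures and both follow-up visits have equal standing. A reader of the eventual report could not tell whether a significant result was the one the trial was set up to examine or one of many that happened to fall below the threshold. What is at stake is the interpretability of the trial's main conclusion.

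**Working it through.** The protocol states no alpha, power or familywise error rate, so it has no figure of its own to reproduce. The check asks how often the stated rule yields at least one significant between-arm difference when the device has no effect.

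**Inputs**
- Measures: METHODS gives trunk angle, centre of mass, COP, FRT, Berg, falls, FES, PDQ-39, UPDRS II and UPDRS III. That is 10, taking one variable per measure.
- Follow-up visits: 2 (METHODS).
- Arm size: 18 (STUDY DESIGN: "The study is expected to enroll approximately 36 patients"). STATISTICAL ANALYSIS speaks of 40 participants; the independence results do not depend on arm size.
- Assumed: two-sided alpha 0.05 per test, and a separate test at T1 and at T2. The second is inferred by reading STATISTICAL ANALYSIS with METHODS.

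**Number of between-arm tests:** 10 × 2 = 20.

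**Independent tests**
- Any difference: 1 − 0.95^20 = 0.642.
- A difference favouring the device: 1 − 0.975^20 = 0.397.

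**Correlated tests.** Measures on the same patients will be correlated, so null trials were simulated with 18 per arm and 20 two-sample t-tests sharing one pairwise correlation.

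| Correlation | Any false positive | Favouring the device |
|---|---|---|
| 0 | 64% | 40% |
| 0.5 | 43% | 21% to 22% |
| 0.7 | 30% | 15% |
| Single test, for comparison | 5% | 2.5% |

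With separate correlations for outcomes and visits the picture is similar: 44% to 47% with outcomes at 0.5 and visits at 0.5 to 0.7, and 32% with outcomes at 0.7 and visits at 0.8.

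**Expected number of false positives:** 20 × 0.05 = 1, of which 20 × 0.025 = 0.5 favour the device. Correlation does not change these expectations.

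**Sensitivity to the count**
- Counting only the seven bullets in METHODS gives 7 × 2 = 14 tests: 1 − 0.95^14 = 51% if independent, and 36% to 38% with outcomes at 0.5.
- If the platform measures and PDQ-39 each yield several variables and the total reaches 20, there are 40 tests: 1 − 0.95^40 = 87% if independent, and 62% to 64% with outcomes at 0.5.

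**Within-arm tests.** Paired comparisons from T0 to T1 and T0 to T2 in both arms would add 10 × 2 × 2 = 40 tests. They are left out. STUDY DESIGN gives both arms physiotherapy, so an inert device does not imply zero change from baseline, and a significant within-arm change may be a real effect of physiotherapy.

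**Power of a single primary test.** By the normal approximation, the standardised difference detectable with 80% power at 18 per arm is (1.960 + 0.842) × √(2/18) = 2.802 × 0.333 = 0.93. Power is about 80% at 0.94, 67% at 0.8 and 32% at 0.5.

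**The case against.** The strongest reply is that this is a pilot. The protocol calls the study pilot and preliminary, asks only whether the device may be effective, and says "This clinical trial will use a sample of convenience, with the assumption that 40 participants would be ample to explore safety and feasibility". That lowers the weight of the point, and it would be wrong to read the objective as a confirmatory claim. It does not remove the point, because the objectives concern effect on balance, posture and falls, and significance testing is the stated method.

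A second reply is that a multiplicity rule may sit in a statistical analysis plan that is not at hand. This stands: the protocol alone does not show that the trial leaves its error rate uncontrolled. The choice of primary outcome and visit, however, belongs in the protocol, and the protocol's own rule gives every variable equal rank.

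A third reply is that the count of 20 is built from assumptions. This also stands. STATISTICAL ANALYSIS does not list the visits to be tested, and if the initial ANOVA acts as a gate for each variable, fewer t-tests would follow. The text does not settle this.

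Two stronger readings are tempting. A reader might infer that a false device effect is more likely than not. At 20 tests that holds only for a difference in either direction and only at low correlation; for a result favouring the device, the chance stays below one half throughout. A reader might also add the within-arm tests and expect 3 to 4 false positives (60 to 80 tests × 0.05). That assumes no change under physiotherapy, which the design gives no reason to expect.

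**Conclusion.** The point holds as a missing primary comparison combined with a rule to test everything. Under the two stated assumptions, the chance of at least one spurious between-arm difference is roughly 30% to 64% over correlations from 0.7 down to 0. The chance of one favouring the device is roughly 15% to 40%, that is, 6 to 16 times the 2.5% of a single test (15/2.5 and 40/2.5). The within-arm comparisons have a different weakness: they cannot separate the device from physiotherapy, whatever their p-values. The pilot status and a possible rule in an unseen analysis plan make the point less severe, but the primary comparison still needs to be named.

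**What to change.** Before unblinding, name in the protocol one primary between-arm comparison at one visit. One option is the Berg Balance Scale at T1, adjusted for T0, at two-sided 5%. The trunk inclination angle at T1, defined as a single measure, could come second in a fixed sequence; this covers balance and posture at a familywise 5%. Nothing in the protocol ranks these measures first, so the sponsor may choose others.

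State that T2 (which addresses maintenance), falls and all remaining variables are secondary or exploratory, reported as estimates with 95% confidence intervals. The example sequence does not cover those parts of the objective, and the text should say so. State also that within-arm tests do not support a claim about the device.

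The change takes a few sentences and alters no visit, measurement or treatment. A nominally significant exploratory result could then no longer support an efficacy claim. Because 18 per arm has about 80% power only for a standardised difference near 0.94, a non-significant primary result would leave moderate effects open, and the pilot's conclusions should be worded accordingly.

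### Within-arm and between-arm t-tests are planned side by side on all variables and neither is named as decisive, although both arms receive physiotherapy and only the between-arm contrast can isolate the device

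*Protocol*

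**What the plan says.** The Statistical Analysis section of the protocol states: "A comparison will be made for all variables". The comparisons are to be made "for dependent samples for independent samples to evaluate both the variation within the group than those between the two groups", and the section adds: "This will be done through the use of a T- test". So a paired test inside each arm and a two-sample test between the arms are both planned, on every variable. An ANOVA is listed ahead of them. The section does not rank the two kinds of t-test, does not attach either to a visit, and does not say whether the between-arm test uses changes or final values.

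The Study Design section gives the arms as "18 patients Experimental Group E-PT ( Equistasi + Physical Therapy") and "18 patients Group Control P -PT ( Placebo + Physical Therapy"). The control arm receives "similar physiotherapy treatment plus an inactive device (placebo) , of the same duration and frequency of the first group".

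The Background section frames the aim as comparative: whether adding the device does better than physiotherapy alone. The Objective section asks whether the device helps "in improving balance and posture alterations and in maintenaning the outcome". The Methods section schedules assessments at T0, T1 (after 8 weeks of treatment) and T2 (8 weeks later). No criterion, margin or test for maintenance is given.

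**The concern.** Physiotherapy is the active component that the two arms share, so patients in both may improve from T0 even if the device does nothing. A paired test inside the Equistasi arm asks whether those patients changed. It cannot divide the change between physiotherapy and device. Setting a significant result in one arm against a non-significant result in the other does not repair this, because a difference in significance is not a test of a difference. Only the randomised contrast answers the comparative aim.

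The plan gives the two kinds of test equal standing. With 18 per arm the between-arm test is weak, so significant within-arm results beside a non-significant between-arm result are a realistic outcome. The protocol has no rule for which of them the conclusion should follow.

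Maintenance raises a similar problem. It is an objective without a named test, and the only within-arm tool listed is the paired t-test. A non-significant change from T1 to T2 in 18 patients would say little about whether the gain was kept.

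**Working it through.** The protocol gives no numerical alpha, power, SD or effect size, so it has no figure of its own to reproduce on this point. The calculation shows how the listed tests behave at the planned size.

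**Inputs**
- From Study Design: n = 18 per arm.
- Assumed: two-sided alpha 0.05, normally distributed changes, no dropout, no device effect, and the same true improvement in both arms.
- Assumed range for that improvement: dz = mean change / SD of change = 0.3, 0.5, 0.8.

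**Step 1: paired test in one arm.** The statistic follows a noncentral t distribution with 17 degrees of freedom and noncentrality dz × √18. Let p be the probability of significance.
- dz 0.3: noncentrality 0.3 × 4.243 = 1.27, p = 0.225
- dz 0.5: noncentrality 0.5 × 4.243 = 2.12, p = 0.516
- dz 0.8: noncentrality 0.8 × 4.243 = 3.39, p = 0.892

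**Step 2: significant with Equistasi, not with placebo.** The arms are independent and p is the same in both, so the probability is p × (1 − p).
- dz 0.3: 0.225 × 0.775 = 0.174
- dz 0.5: 0.516 × 0.484 = 0.250
- dz 0.8: 0.892 × 0.108 = 0.096

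Simulation with 100,000 trials per scenario gave 0.177, 0.250 and 0.095.

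**Step 3: between-arm test of change in the same simulated trials.** It was significant in 5.1%, 5.0% and 5.0%, so about 2.5% in the device's favour, whatever the physiotherapy effect. The pattern in step 2 is therefore about 0.096 / 0.025 ≈ 4 to 0.250 / 0.025 = 10 times as frequent.

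**Step 4: power of the valid test.** At 18 per arm the between-arm t-test reaches 80% power only for a difference of about 0.96 SD. For a difference of 0.5 SD its power is 31%.

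**Step 5: paired test from T1 to T2, if it were used for maintenance.** The formula is that of step 1, with dz now the true loss. A non-significant result has probability 1 − p:
- loss 0.3 SD: 1 − 0.225 = 0.775, about 78%
- loss 0.5 SD: 1 − 0.516 = 0.484, about 48%
- loss 0.8 SD: 1 − 0.892 = 0.108, about 11%

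A loss of about 0.70 SD is needed for 80% power.

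**Sensitivity to sample size.** The Statistical Analysis section mentions 40 participants, against about 36 in Study Design. With 20 per arm, p is 0.246, 0.564 and 0.924. Step 2 then gives 0.246 × 0.754 = 0.185, 0.564 × 0.436 = 0.246 and 0.924 × 0.076 = 0.070. The conclusion is the same.

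**The case against.** The strongest reply is that the valid comparison is already in the plan. The sentence that provides for dependent samples also provides for independent samples, and the aim and the placebo-device control are comparative. A reader might infer that efficacy will be judged by paired tests alone and that the randomised control is discarded. The text does not support that.

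A reader might also infer that significance in one arm only will count as proof of the device, or that a non-significant change from T1 to T2 will be read as maintenance. The protocol states neither rule and names no T1-T2 test. This stands, and the rates above are therefore conditional: they show what those readings would cost if they were adopted.

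The sizes depend on assumed effects. The step 2 rate peaks near 0.5 SD and falls to 10% at 0.8 SD. The maintenance figure falls from 78% to 11% over the range shown. Normal changes are assumed, whereas the section itself says most variables are not normally distributed. These points also stand, which is why ranges are given.

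A statistical analysis plan that is not shown could rank the tests, and details such as covariate adjustment are often left to it. This stands only in part. The protocol has not merely left the matter open: it assigns inferential within-arm tests to every variable, on a par with the randomised comparison. Finally, the study is a pilot with a convenience sample. That lowers the severity, but it also favours estimates with intervals over many within-arm p-values.

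**Conclusion.** The point holds as a fault of hierarchy. The between-arm comparison is present; what is missing is any statement that it decides, while tests that cannot isolate the device stand beside it with equal weight.

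If arm-by-arm significance were used to judge an ineffective device, about 10-25% of trials per outcome would show the misleading pattern in its favour, against 2.5% for the between-arm test. For maintenance, a non-significant paired test would be weak evidence unless the true loss were large. All of these figures rest on the assumptions listed in the working; only n = 18 per arm comes from the protocol.

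Severity is should-fix. The study is a pilot and already plans a between-arm test, so a clear ranking of the analyses is enough.

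**What to change.** State in the Statistical Analysis section that:

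- conclusions about the device rest on the between-arm difference adjusted for the T0 value, at T1 for efficacy and at T2 for whether the device's advantage persists, each with a 95% CI;
- the between-arm difference in change from T1 to T2 is reported as an estimate, because the T2 difference alone does not show how much of the T1 gain was kept;
- within-arm changes are presented descriptively and are not evidence of device efficacy or of maintenance.

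The chosen method should agree with the section's own statement that most variables are not normally distributed, for example through a rank-based or bootstrap version of the adjusted comparison.

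The cost is a change of wording before the data are seen. It needs no extra patients, visits or measurements, and leaves fewer tests to run.
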